## Abstract

**Background:**

Acute mountain sickness (AMS) poses a unique and formidable challenge to healthy personnel at high altitudes.

**Objective:**

This randomized controlled trial (RCT) protocol aimed to assess the effectiveness of Ayurvedic nutritional supplements in conjunction with a yoga protocol in reducing the incidence and severity of AMS among healthy personnel stationed in the challenging high-altitude landscapes of the western Himalayas.

**Methods:**

The proposed open-label, parallel-group RCT was conducted in apparently healthy individuals of any gender aged 18‐50 years. The study was conducted at two distinct high-altitude stages within the western Himalayan region: stage I, situated at an elevation ranging from 9000 to 12,000 feet and stage II, spanning 12,000 to 15,000 feet. A total of 1660 participants (n=830 per stage) underwent random assignment in a 1:1 ratio to receive either the existing acclimatization schedule (AS) for high altitude (control group) or the Ayush intervention (Ayush group) in addition to the AS. The participants in the Ayush group received Ayurvedic nutritional supplements, including the Ayur-nutri kit (Ayush poshak yoga, 25 g, and Ayush cardiac care tea, 125 mL), twice daily, along with a yoga protocol (60 min daily) for 120 days. The primary outcome was the incidence of AMS, assessed using the 2018 Lake Louise Scoring System, and the proportion of participants with a Lake Louise Scoring System score of 6 or higher during the first 7 days from baseline. The secondary outcome measures included the proportion of participants with thromboembolic events; changes in coagulation and hemostasis activation markers and proinflammatory markers; and changes in self-reported negative emotional states (depression, anxiety, and stress), sleep quality, and overall quality of life (assessed through Depression Anxiety Stress Scale-21 items, Pittsburgh Sleep Quality Index, and 12-item short-form, respectively) on day 60 and day 120 from baseline.

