## Introduction

### Background

High-altitude illness (HAI) is the collective term used for various debilitating health conditions that can affect individuals who are not acclimatized and ascend rapidly to high altitudes within 6 to 12 hours of their ascent to high altitude [1,2]. Conventionally, 2500 meters has been used as the threshold for HAI [2]. The spectrum of HAI encompasses various conditions that can range from mild to severe, among which the most typical are acute mountain sickness (AMS), high-altitude cerebral edema, and high-altitude pulmonary edema (HAPE). High-altitude cerebral edema and HAPE occur much less frequently than AMS but are potentially fatal. The risk factors for HAI are the rate of ascent, high altitude reached (especially the sleeping altitude), previous high-altitude exposure, and individual susceptibility [1,3,4]. AMS is a common clinical presentation in individuals venturing over 2500 meters and above [5]. The prevalence and severity of AMS rise with increasing altitude. It occurs in approximately 10% to 25% of nonacclimatized individuals at 2500 meters, which may increase to 50% to 85% at an altitude of 4500 to 5500 meters [2,6-8]. The pathophysiology of AMS includes relative hypoventilation, impaired gas exchange, increased sympathetic activity, fluid retention and redistribution, and raised intracranial pressure in case of moderate to severe AMS [1,5]. AMS presents with a group of nonspecific symptoms such as headache (primary defining symptom), gastrointestinal symptoms (anorexia, nausea, or vomiting), fatigue and/or weakness, dizziness, or disturbed sleep [9].

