### Study Intervention

The eligible participants in the Ayush group (AG) received a comprehensive Ayush-AMS protocol, which included the use of an Ayur-nutri kit and a yoga protocol, along with the existing AS, for 120 days while staying in high-altitude regions [27].

The Ayur-nutri kit contains 2 herbal products, viz, an Ayurvedic nutritional supplement, Ayush poshak yoga, and an herbal tea, Ayush CCT, developed by the Central Council for Research in Ayurvedic Sciences, Ministry of Ayush, Government of India, to address nutritional supplementation requirements and to maintain healthy well-being at high-altitude regions. The Ayush poshak yoga powder contains a diverse blend of nuts and seeds, including cashews, almonds, pistachios, walnuts, pumpkin seeds, and cucumber seeds. It also contains herbs such as *W. somnifera* (L.) Dunal, *P. longum* L., *T. cordifolia* (Willd.) Miers ex Hook.f, *P. nigrum* L.*, Z. officinale* Roscoe., *Foeniculum vulgare* Mill., renowned for their nutritional and therapeutic benefits (Table 1). The Ayush CCT is a novel herbal tea that combines the heritage of traditional tea with a blend of herbal ingredients, including *T. arjuna* (Roxb.). Wight & Arn, saffron, cardamom, and cinnamon that can promote cardiovascular health, overall well-being, and healthy circulation (Table 1). Ayush CCT was made into an infusion by dipping one Ayush CCT tea bag in 125 mL of hot water for 5 minutes, allowing for an appropriate steeping time, and then used warm. Ayush poshak yoga was given in a dose of 25 g twice daily (morning and evening, 1 h before meals), along with 125 mL of Ayush CCT.

**Table 1. T1:** Details of ingredients of Ayush poshak yoga and Ayush CCT^a^.

Ayur-nutri kit and ingredients (botanical/English name)	Part used
Ayush poshak yoga	
*Anacardium occidentale* L. (Cashew nut)	Kernel
*Prunus amygdalus* Stokes (Almond)	Kernel
*Pistacia vera* L. (Pistachio)	Kernel
*Juglans regia* L. (Walnut)	Cotyledons
*Papaver somniferum* L.	Seed
*Chlorophytum borivilianum* Santap & R.R.Frn	Tuberous root
*Cucumis melo* L.	Seed
*Cucumis sativus* L.	Seed
*Citrullus vulgaris* Schrad.	Seed
*Cucumis melo* var. *utilissimus* Dutt & Fueller	Seed
*Zingiber officinale* Rosc	Rhizome
*Piper longum* L.	Fruit
*Piper nigrum* L.	Fruit
*Withania somnifera* (L.) Dunal.	Root
*Foeniculum vulgare* Mill.	Fruit
*Tinospora cordifolia* (Willd.) Miers	Stem
Sugar candy	
Excipients, preservatives, flavoring agents (approved)	
Ayush CCT	

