### Outcome Measures

The primary outcome was the incidence of AMS, assessed using the 2018 Lake Louise Scoring System (LLSS). AMS is defined as an LLSS score of 3 or more points from the 4 rated symptoms (headache, nausea or vomiting, fatigue, and dizziness or light-headedness), including at least 1 point from headache [9]. The grading of LLSS score is mild AMS 3‐5 points, moderate AMS 6‐9 points, and severe AMS 10‐12 points [9]. The participants were assessed daily for the first 7 days at the stage I high-altitude areas using the LLSS score to record the incidence and evaluate the severity of AMS. The primary outcome will be reported as the proportion of participants who display symptoms of AMS and the proportion of participants with a score of more than 6 as per the LLSS. The participants enrolled for stage II were again assessed daily during their first 4 days at that altitude for the incidence and severity of AMS.

The secondary outcome measures included the proportion of participants who developed thromboembolic events (deep-vein thrombosis, pulmonary embolism, cerebral venous thrombosis, myocardial infarction, etc) during the study, change in the levels of markers of coagulation and hemostasis activation (total red blood cell count, hemoglobin, packed cell volume, D-dimer, lactate dehydrogenase, creatine kinase, creatine kinase-myocardial band, fibrinogen, activated partial thromboplastin time, prothrombin time), changes in the levels of proinflammatory markers (high sensitivity C-reactive protein, interleukin-6, tumor necrosis factor-α); self-reported changes in negative emotional states of depression, anxiety, and stress assessed through Depression Anxiety Stress Scale-21 item (DASS-21); change in sleep quality assessed through the Pittsburgh Sleep Quality Index (PSQI), and quality of life assessed through the 12-item short-form (SF-12) questionnaire. The secondary outcomes were evaluated on day 60 and day 120 from baseline. However, the participants enrolled for the stage II high-altitude area were also assessed on day 10 (day 4 of the AS at that altitude) and on the day of descent, in case of early descent before day 120.

Resting heart rate, systolic and diastolic blood pressure, respiratory rate, and oxygen saturation (SpO2) were also documented daily until day 7, alongside LLSS at stage I high altitude, and until day 10 in participants at stage II high altitude. These measurements were then taken on scheduled follow-up visits.

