### Recruitment of Study Participants

During the study, the database of healthy personnel in high-altitude areas of the western Himalayan region was used to identify and recruit potential subjects. The investigators at the study site screened subjects based on the defined inclusion and exclusion criteria. The eligible participants were allocated to either of the 2 groups based on a computer-generated randomization schedule. The screening process was continued until the target sample size for the study was achieved.

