### Allocation Concealment

Sequentially numbered, opaque, sealed envelopes were used to ensure allocation concealment. The participant’s enrollment number was printed at the top of the envelope, and a slip indicating the participant’s allocated group was kept inside. After completing all baseline assessments, the research staff provided the sealed envelope to the eligible participant. The participant opened the envelope and was then assigned to the group as indicated on the slip inside. The opened envelope and the printed slip were attached to the participant’s CRF for record and trial monitoring.

Participants assigned to the 2 study groups were housed in separate barracks throughout the study to prevent any protocol violations and minimize the risk of contamination bias. Further, yoga sessions and supplement distribution were conducted at designated areas accessible only to the intervention group, with attendance monitored by site instructors. The CG did not receive access to these sessions or materials, reducing the likelihood of unintentional participation. Study staff members were instructed to avoid sharing intervention-related information with control-group participants.

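### AMS already present at the baseline Lake Louise assessment can count as an incident primary event, because no printed rule uses that baseline score

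*Protocol article*

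**What the plan says.** - **Window.** The Abstract's Methods paragraph names AMS incidence and the proportion with a "score of 6 or higher during the first 7 days from baseline". Outcome Measures gives the window by place: "The participants were assessed daily for the first 7 days at the stage I high-altitude areas using the LLSS score".
- **What is counted.** "The primary outcome will be reported as the proportion of participants who display symptoms of AMS". The case definition is "AMS is defined as an LLSS score of 3 or more points from the 4 rated symptoms", with at least 1 point from headache. Neither sentence requires that the participant was free of AMS at baseline.
- **Baseline measurement.** Table 3 (Data Collection) schedules the LLSS at baseline, in a column separate from days 1 to 7.
- **Order of events.** Allocation Concealment: "After completing all baseline assessments, the research staff provided the sealed envelope to the eligible participant". AMS status is therefore recorded before allocation.
- **Eligibility.** Study Participants requires people who are apparently healthy and fit for the sojourn. It has a discretionary, safety-based exclusion for other conditions, but no exclusion for currently meeting the AMS definition.
- **Analysis.** Statistical Methods compares proportions by chi-square. The baseline variables it gives as examples for adjustment are age, prior altitude exposure and hydration indicators; baseline LLSS is not named.

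**The concern.** The trial asks whether the intervention prevents AMS. A case present before allocation cannot be prevented by what is allocated. Suppose a participant has headache and a score of 4 at baseline and scores 4 again on day 1. The baseline score need not be counted itself: persistence to day 1 is enough to meet the printed definition.

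Several statements make this possible. The Background places high-altitude illness in unacclimatized people who "ascend rapidly to high altitudes within 6 to 12 hours of their ascent to high altitude". Under Recruitment, "the database of healthy personnel in high-altitude areas of the western Himalayan region was used to identify and recruit potential subjects". The intervention was given "for 120 days while staying in high-altitude regions", and no pre-ascent period is described. If baseline took place some hours after arrival, some participants could already have had AMS.

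At stake are the meaning and the sensitivity of the primary result. Non-preventable events in both arms shrink the risk difference and move the risk ratio towards 1. A null finding would be harder to interpret, and the reported proportion would not strictly be an incidence.

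**Working it through.** **Inputs.** From Sample Size: 25% in controls, 18% in the Ayush group (risk ratio 18/25 = 0.72), 90% power, a 95% confidence level (read as two-sided alpha 0.05), and 722 per group before attrition. Assumed, because the article does not give it: a fraction *f* with AMS at baseline, equal in both arms, all persisting into the window and unaffected by treatment. Values of 2, 5 and 8% are illustrations.

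**The plan's own figure.** With pooled variance and no continuity correction,
n = [1.960·√(2·0.215·0.785) + 1.282·√(0.25·0.75 + 0.18·0.82)]² / 0.07² = 721.8, rounded up to 722. Power at 722 is 90.0%, so the stated figure reproduces.

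**Model A: 25% and 18% are risks among AMS-free participants, with prevalent cases added on top.**
Rates counted: f + (1−f)·0.25 and f + (1−f)·0.18, so the difference is 7.0·(1−f) points. With baseline positives removed, the rates return to 25% and 18% on 722·(1−f) per arm.

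| f | Control | Ayush | Difference (points) | Risk ratio | Power, all counted | Power, positives removed |
|---|---|---|---|---|---|---|
| 2% | 26.5% | 19.6% | 6.9 | 0.74 | 87% | 89% |
| 5% | 28.8% | 22.1% | 6.7 | 0.77 | 83% | 88% |
| 8% | 31.0% | 24.6% | 6.4 | 0.79 | 78% | 87% |

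**Model B: the planned 25% already includes f, and 0.72 applies only to new cases.**
Ayush rate counted: f + (0.25−f)·0.72. With positives removed, the control rate is (0.25−f)/(1−f), the risk ratio is 0.72, and there are 722·(1−f) per arm.

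| f | Control | Ayush | Difference (points) | Risk ratio | Power, all counted | Power, positives removed |
|---|---|---|---|---|---|---|
| 2% | 25% | 18.6% | 6.4 | 0.74 | 84% | 87% |
| 5% | 25% | 19.4% | 5.6 | 0.78 | 73% | 81% |
| 8% | 25% | 20.2% | 4.8 | 0.81 | 58% | 73% |

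At f = 0 nothing changes. In every row, removing baseline positives raises power and restores the risk ratio of 0.72.

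**Calendar check.** Outcome Measures equates study day 10 with day 4 of acclimatization at stage II. The Discussion gives 6 days for stage I acclimatization and a further 4 for stage II: 6 + 4 = 10. Study day 1 therefore appears to coincide with acclimatization day 1, which puts baseline near arrival. The hour, and whether baseline came before or after ascent, are not stated.

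**The case against.** The strongest objection is that nothing shows prevalent cases exist. The calendar puts baseline near arrival, and if onset takes hours after ascent, most AMS would begin after baseline. The requirement to be apparently healthy and fit for the sojourn makes enrolling someone with current AMS less likely. The recruitment database says where candidates were found, not when baseline was done. All of this stands, and it is why the effect may be small.

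A reader might infer that prevalent cases are in fact counted as events, or that the baseline score itself enters the numerator. The documents support neither: Table 3 keeps baseline apart from days 1 to 7. What the text supports is that a baseline case persisting to day 1 can count.

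The article is also condensed, its list of adjustment variables is illustrative, and a rule may exist in a fuller document. That limits any complaint about missing detail. But the article does state its endpoint, window, case definition and eligibility, and taken together these admit baseline-positive participants.

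On size, the prevalences are assumptions, and Model B alone would give too severe a picture. All 1660 participants were enrolled; with 830 per arm and no loss, planned power is 93.5%, and Model B at 2% still gives about 89%. Finally, changing the primary definition after data collection in an open-label trial invites a charge of post hoc choice. That is a real cost, to be met by timing and documentation.

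**Conclusion.** The point holds as a gap in the printed endpoint definition. AMS present at the baseline LLSS and persisting to day 1 meets the definition of an incident case, and the baseline score that would identify it has no stated use. The consequence is dilution of the risk difference and lost power. It is not between-arm bias, because the status is fixed before allocation and balanced in expectation.

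The size cannot be fixed from the article. For assumed prevalences of 2 to 8% at 722 per arm, power falls from 90% to between 87% and 78% (Model A) or between 84% and 58% (Model B). These figures assume that every baseline case persists and that treatment does not affect it. If baseline was before or at ascent, the loss may be negligible. A reader might conclude that the trial is materially underpowered for this reason; the documents do not support that.

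**What to change.** Set the following before any arm-level results are seen:

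1. State when baseline occurred relative to ascent, and how many randomised participants met the AMS definition at the baseline LLSS (both arms pooled). If none did, one sentence closes the matter.
2. Define incident AMS as first meeting the criteria (LLSS of 3 or more with headache of at least 1) after allocation, among randomised participants who do not meet them at baseline.
3. Add baseline LLSS to the adjustment variables.
4. Report the all-randomised result, baseline positives included, alongside.

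The baseline LLSS is already scheduled and the analysis is in progress, so no new data are needed for steps 2 to 4. Restricting on a value recorded before allocation keeps the randomised comparison intact. The costs are a slightly smaller denominator (at 5%, about 686 of 722 per arm) and the need to document openly that the definition was set after data collection ended.

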**Results:**

The study was funded in March 2023. The data collection was completed in December 2023. A total of 1660 participants were enrolled in the study. The analysis of the study data is in progress. The study outcomes are expected to be published by December 2026.

**Conclusions:**

This RCT was the first of its kind to explore the potential benefits of using Ayurvedic nutritional supplements and a yoga protocol in conjunction with the standard AS to reduce the occurrence and severity of AMS among healthy personnel. The outcomes of this trial can aid in better acclimatization and resilience among healthy personnel at high altitudes.

## Introduction

### Background

High-altitude illness (HAI) is the collective term used for various debilitating health conditions that can affect individuals who are not acclimatized and ascend rapidly to high altitudes within 6 to 12 hours of their ascent to high altitude [1,2]. Conventionally, 2500 meters has been used as the threshold for HAI [2]. The spectrum of HAI encompasses various conditions that can range from mild to severe, among which the most typical are acute mountain sickness (AMS), high-altitude cerebral edema, and high-altitude pulmonary edema (HAPE). High-altitude cerebral edema and HAPE occur much less frequently than AMS but are potentially fatal. The risk factors for HAI are the rate of ascent, high altitude reached (especially the sleeping altitude), previous high-altitude exposure, and individual susceptibility [1,3,4]. AMS is a common clinical presentation in individuals venturing over 2500 meters and above [5]. The prevalence and severity of AMS rise with increasing altitude. It occurs in approximately 10% to 25% of nonacclimatized individuals at 2500 meters, which may increase to 50% to 85% at an altitude of 4500 to 5500 meters [2,6-8]. The pathophysiology of AMS includes relative hypoventilation, impaired gas exchange, increased sympathetic activity, fluid retention and redistribution, and raised intracranial pressure in case of moderate to severe AMS [1,5]. AMS presents with a group of nonspecific symptoms such as headache (primary defining symptom), gastrointestinal symptoms (anorexia, nausea, or vomiting), fatigue and/or weakness, dizziness, or disturbed sleep [9].

A gradual ascent to enable acclimatization is usually impractical logistically for individuals susceptible to AMS, particularly in recreational, tactical, and exigency situations. Considering this limitation, several clinical studies have been conducted over the last 2 decades to explore the efficacy of conventional medications in reducing the incidence of AMS, followed by a few systematic reviews [10-13]. The interventions, such as acetazolamide, dexamethasone, and ibuprofen, have shown promising results in reducing the severity of AMS; however, they have specific adverse effects, limiting their routine use. Acetazolamide has reported adverse effects, including headache, nausea, polyuria, and dysgeusia [11,12]. Similarly, dexamethasone and ibuprofen have shown adverse effects such as gastrointestinal symptoms, headache, skin rashes, edema, and mood changes (including depression) [12]. Considering this, exploring effective, safe, and readily available interventions for prophylaxis and management of AMS is essential.

Ayurveda, the traditional Indian medicine, aims to improve the quality and span of life, primarily emphasizing disease prevention and health promotion by strengthening body tissues to withstand both exogenous and endogenous stressors. The same can be achieved by modulating diet and lifestyle and by using Ayurvedic nutritional supplements (containing herbal ingredients) such as *Rasayana*, which help restore the body’s equilibrium. The herbal ingredients used in Ayurvedic nutritional supplements are known for their adaptogenic, antioxidant, and immunomodulatory properties [14-16]. A holistic approach involving the use of Ayurvedic nutritional supplements and a yoga protocol may have significant scope for reducing AMS, effectively addressing psychological and physiological well-being, considering that while the Ayurveda supplements enable the body to cope with the physical stressors, the yoga protocol can enhance the mental resilience and focus, which are crucial for operating in challenging conditions.

### Rationale for Study Interventions

The Ayur-nutri kit comprises Ayush poshak yoga, a nutritional supplement, and Ayush cardiac care tea (CCT), an herbal drink, having ingredients such as *Terminalia arjuna* (Roxb.) Wight & Arn*, Crocus sativus* L.*, Withania somnifera* (L.) Dunal*, Tinospora cordifolia* (Willd.) Miers ex Hook.f*, Zingiber officinale* Roscoe*, Piper longum* L.*, Piper nigrum* L.*, Chlorophytum borivilinium* Santapau & R.R.Fern., etc, along with a wide variety of nuts and seeds such as almonds, walnuts, cashews, pistachios, pumpkin seeds, and melon seeds. The herbs in these nutritional supplements have cardioprotective, neuroprotective, hepatoprotective, antihypertensive, antidyslipidemic, anti-inflammatory, antiatherogenic, antiplatelet aggregation, antithrombotic, and anticoagulant activities [17-21]. A clinical study on these nutritional supplements, conducted among volunteers of the Antarctica expedition, reported significant improvements in stress-related changes in immunoglobulins and antioxidant enzymes, alongside an enhanced quality of life. This suggests that they are effective in managing cold stress and were also found to be safe [22]. Preliminary studies have shown that yoga contributes to acclimatization at high altitude and plays a crucial role in maintaining physical fitness and mental resilience [23]. Respiratory adaptations induced by yoga may offer an efficient strategy to cope with high altitude–induced hypoxia [24,25].

Based on the evidence stated above, this study has been conceptualized to assess the comparative effectiveness of incorporating a combined protocol of Ayurvedic nutritional supplements and yoga alongside the existing acclimatization regimen for preventing AMS among healthy personnel at high-altitude terrains.

